### **5.3.7 Mood symptoms**

*HADS* - The Hospital Anxiety and Depression Scale (HADS) is a self-assessed questionnaire consisting of 14 multiple-choice (0–3 Likert scale) items probing symptoms of anxiety (7 items) and depression (7 items). HADS anxiety (HADS-A) and depression (HADS-D) scores range from 0 (no symptoms) to 21 (most severe symptoms) [Zigmond 1983]. We choose HADS because it is a screening tool with robust psychometric properties, and has been validated in several languages, including Italian [Costantini 1999]. Furthermore, by omitting items assessing somatic symptoms, and thereby limiting false positive findings, the scale is suitable for use in persons with medical conditions [Herrmann 1997]. A cutoff score of 8 or above was recommended for MS patients, since it was found to be an accurate indicator of major depression (90% sensitivity, 87% specificity) and generalized anxiety disorder (88.5% sensitivity; 81% specificity) in this population [Honarmand 2009]. We will use the Italian version of the HADS [Costantini 1999].

### **5.3.8 Safety data monitoring plan**

A thorough safety data monitoring plan will be developed and implemented in order to monitor participant safety, as well as data integrity. Adverse events (AEs) will be recorded by the site and reported to the PI immediately.

For the *ConCure-SM* Phase 2 study, a Serious Adverse Event (SAE) will be defined as an emotional breakdown resulting in hospitalization, suicidal attempt, or death. AEs will include the following: a) any contact to the patient referring physician due to the occurrence of emotional problems during the study; b) an increase of  $\geq 20\%$  in the HADS Anxiety or/and depression score [Puhan 2008]. AEs will be monitored to ensure that the AE was caused by the study intervention, and not some coincidental issue. AEs will be collected and reported to the study PI as well as the DMSC.

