## 5.2 Pilot study

### 5.2.1 Study design

Multi-center, pilot and feasibility mixed-methods study. It is a non-randomized study (all participants will receive the intervention).

The six centers involved are located in northern (four centers), central and southern Italy (one center each). Two of the centers are rehabilitation hospitals (one of which a research hospital), three are MS centers (two university hospitals, one research hospital) and one is a rehabilitation and MS center from a research hospital.

Recruitment will be competitive, with no pre-specified minimum number of enrolled subjects per center. The maximum number of enrolled subjects per center is 12.

There will be a baseline assessment (T0), an ACP conversation taking place within one month from the baseline assessment, and a follow-up assessment within one week of the ACP conversation (T1) and six months (T2) thereafter. The baseline and follow-up assessments will be performed via the web-based [ConCure-SM](#) platform.

**Table 1.** Summary of trial procedures

|                                         |                                                                                                                                                                                                                                                                                                                                             |                                                                                                                                                                          |
|-----------------------------------------|---------------------------------------------------------------------------------------------------------------------------------------------------------------------------------------------------------------------------------------------------------------------------------------------------------------------------------------------|--------------------------------------------------------------------------------------------------------------------------------------------------------------------------|

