### 5.2.2 Participant eligibility

We chose to focus our study population on pwPMS, as evidence suggests that patients may be less likely to engage in ACP if they perceive themselves as 'too healthy' [Schickedanz 2009].

PwPMS (in- or outpatients) will be included if they:

- Are ≥18 years of age;
- Were diagnosed with primary or secondary PMS [Lublin 1996] from one or more years before inclusion;
- Are able to communicate in Italian;
- Gave written consent;
- Have one or more of the following conditions that would make ACP relevant:
  - Express desire for ACP;
  - Raise questions about their future;
  - Talk about hastening death or medically assisted suicide;
  - High risk for death within two years using the 'Surprise Question' [Downar 2017];
  - High risk for development of severe cognitive compromise/dementia within two years;
  - High risk for development of impairments preventing communication within two years;
  - Significant suffering (e.g. uncontrolled physical symptoms, psychosocial or existential issues).

PwPMS will be excluded if they have one or more of the following:

- Severe cognitive compromise (MMSE < 19) or impairments preventing communication;
- Psychosis or other serious psychiatric conditions;
- Advance care plan document completed.

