### **5.2.3 Recruitment**

PwPMS are recruited prospectively by the ACP-trained physicians involved in their care, when the potentially eligible pwPMS attends the center for an outpatient visit or hospitalization. PwPMS who show interest in participating receive full verbal and written information about the study purpose and procedures.

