### **5.2.4 Baseline assessment (T0)**

The ACP-trained physician makes an appointment with pwPMS who provided initial verbal consent to participate in the study, and checks all eligibility criteria.

A written, signed informed consent is obtained, according to the Declaration of Helsinki and to the Good Clinical Practice (GCP) Guidelines of the EU. The informed consent is kept on file by the study personnel, and is available for inspection by regulatory authorities or authorized persons.

Then, the physician gives the pwPMS the credentials to the trial platform, so that the pwPMS completes the baseline set of questionnaires/instruments (the total assessment will last about 40 minutes). In the event the pwPMS has difficulties in using the trial platform, a phone interview is scheduled within a week with an independent, trained interviewer who will administer the questionnaires/instruments.

The ACP conversation is scheduled at the center, within three weeks. The pwPMS is invited to involve his/her SO (family member, relative, or friend, who is next of kin or is key decision maker as designated by the pwPMS and with whom the pwPMS shares his/her life). If the pwPMS agrees on involving his SO, a SO's telephone number is asked for so that the SO can be contacted by a study researcher to confirm eligibility, explain the study and obtain verbal consent. Consenting SOs receive credentials to access the trial platform and complete the baseline set of questionnaires (completion time about 15 minutes). If the SO has difficulty in using the trial platform, a phone interview is scheduled within a week with an independent, trained interviewer who will administer the questionnaires.

Finally, the physician completes the CRF via the trial platform.

Each center will collect information on the number of pwPMS and SOs approached, screened, and eligible prior to enrollment, with reasons for non-enrolment.

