## 5.3 Outcome Measures

A range of measures will be collected to capture the full process of ACP and whether the *ConCure-SM* intervention has any effect on completion of an advance care plan document (primary outcome measure), congruence in treatment preferences between pwPMS and their carers, quality of patient-clinician communication, and caregiver burden. In addition, since a study-related increase in emotional burden can't be excluded, serious adverse events (SAE: admission to psychiatric ward, suicide attempt, death) will be monitored by the independent Data and Safety Monitoring Committee (DSMC). Mood symptoms will be assessed at baseline and during follow-up.

We are aware that long-term outcomes (chiefly the concordance between preferred and received EOL care and treatments) are warranted. However, the MS trajectory further challenges the collection of this outcome in the typical timeframe of a clinical trial. The assessment of this outcome in pwPMS could be feasible by focusing on the late stages of the disease only. In line with the principles of ACP, we agreed not to narrow the inclusion criteria deserving this relevant outcome to future studies.

We will use the published Italian version of the following inventories: CPS [Giordano 2008], HADS [Costantini 1999], OPTION [Goss 2007], MSQOL-29 [Rosato 2016], ZBI [Chattat 2010].

The 4-item ACP-E and the QOC inventories will be translated and culturally adapted from source language (section 5.3.8).

**Table 2.** Secondary outcome measures of the trial (in alphabetical order)

| Scale name   | Assessor | Construct          | Author       | Italian version | Timing   |
|--------------|----------|--------------------|--------------|-----------------|----------|
| 4-item ACP-E | Patient  | ACP engagement     | Sudore 2017  | –               | T0/T1/T2 |
| eCPS         | Patient  | Role preferences   | Degner 1997  | Solari 2013     | T0       |
| HADS         | Patient  | Mood symptoms      | Zigmond 1983 | Costantini 1999 | T0/T1/T2 |
| MSQOL-29     | Patient  | Health-related QOL | Rosato 2016  | Rosato 2016     | T0/T2    |

| OPTION  | Third observer | SDM (physician's skills)                   | Elwyn 2005     | Goss 2007    | –        |
|---------|----------------|--------------------------------------------|----------------|--------------|----------|
| QOC     | Patient        | Communication quality (physician's skills) | Engelberg 2006 | –            | T1       |

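### Neither SAE definition counts an emotional breakdown that prolongs an existing hospital stay, although inpatients are eligible and recruited

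*Protocol*

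**What the plan says.** Protocol section 5.3.8 fixes the definition: "a Serious Adverse Event (SAE) will be defined as an emotional breakdown resulting in hospitalization, suicidal attempt, or death". Section 5.3 describes the same category differently: "serious adverse events (SAE: admission to psychiatric ward, suicide attempt, death) will be monitored by the independent Data and Safety Monitoring Committee". Neither mentions an existing stay that becomes longer.

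Section 5.2.2 opens eligibility to both settings: "PwPMS (in- or outpatients) will be included if they". Section 5.2.3 places recruitment at the moment "when the potentially eligible pwPMS attends the center for an outpatient visit or hospitalization". Section 5.2.1 adds that "Two of the centers are rehabilitation hospitals"; a further center combines rehabilitation with MS care.

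Events below the SAE threshold are AEs under section 5.3.8. One route is "any contact to the patient referring physician due to the occurrence of emotional problems during the study"; the other is a rise of at least 20% in a HADS score. AEs go to the PI and to the safety committee. Aim 5 in section 3 is to estimate the occurrence of both SAEs and AEs over six months.

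**The concern.** The hospital criterion in section 5.3.8 works only for someone who is outside hospital when the crisis begins. A participant already on a ward cannot, in the ordinary sense, have a breakdown that results in hospitalization. The psychiatric-ward criterion in section 5.3 would catch a transfer to psychiatry, but not a crisis that keeps the participant longer on the same ward.

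At stake is the meaning of the SAE count. Section 5.3 acknowledges that the study may add to emotional burden, and estimating SAE occurrence is a stated aim. Under section 5.3.8, a crisis severe enough to require extra hospital care is serious in an outpatient who is admitted and non-serious in an inpatient whose stay is extended. An estimate that depends on where the participant was when the event began is harder to carry forward to the planned RCT.

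**Working it through.** The protocol gives no SAE rate and no number of inpatients, so there is no figure to reproduce. The check sets the definitions against the population.

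**Step 1. Can a participant be an inpatient when the intervention is delivered?** Inpatients are eligible (5.2.2) and recruited during hospitalization (5.2.3). For timing, section 5.2.4 says: "The ACP conversation is scheduled at the center, within three weeks". Section 5.2.1 allows up to one month from baseline. The conversation can therefore fall within the same stay. The text permits this; it does not say how often it will happen.

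**Step 2. How is each event classified as written?**

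| Event | Section 5.3.8 | Section 5.3 |
|---|---|---|
| Outpatient: breakdown leads to a general-ward admission | SAE | not an SAE |
| Outpatient: breakdown leads to a psychiatric-ward admission | SAE | SAE |
| Inpatient: breakdown leads to transfer to a psychiatric ward | unclear, no new hospitalization | SAE |
| Inpatient: breakdown prolongs the stay on the same ward | **not an SAE** | **not an SAE** |
| Discharged inpatient: breakdown leads to a new admission | SAE | SAE only if psychiatric ward |
| Either setting: breakdown followed by suicide attempt or death | SAE | SAE |

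The fourth row is the gap. Choosing either existing definition over the other leaves it open. The first and fourth rows together show that the difference between settings comes from section 5.3.8. Section 5.3 treats the two alike, but only because it counts no stay outside psychiatry.

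**Step 3. Where does the fourth-row event go?** It can be recorded as an AE through contact with the referring physician or a HADS rise, and is then reported. It does not enter the SAE count.

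**Step 4. How large is the effect?** The number of such events is unknown and may be zero. For scale only: at the planned minimum of 40 participants, one event moved from AE to SAE changes the SAE proportion by 1/40 = 2.5 percentage points.

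**The case against.** There is a serious case that this matters little.

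- **The event is not hidden.** Section 5.3.8 sends AEs as well as SAEs to the PI and the safety committee, and aim 5 estimates both. This stands: the event is classified lower, not lost.
- **The remaining case is narrow.** Suicide attempt and death count in any setting, and psychiatric-ward admission counts under section 5.3. This also stands.
- **Much of the pathway looks outpatient.** The physician makes an appointment (5.2.4), reminders go out about a week before the conversation (5.2.5), and the dedicated slot is justified mainly by pressure on outpatient care (5.1). This weakens any guess at a large inpatient share, but does not remove inpatients from the eligible population.
- **A fuller safety monitoring plan is promised in section 5.3.8.** That does not settle the matter, because the same section already fixes the SAE definition.

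A reader might also infer two stronger conclusions. The first is that every participant who is an inpatient at the conversation drops out of the denominator for the hospitalization component, so that the upper confidence limit for a zero count should rest on fewer participants. The protocol does not support this. SAEs are counted over six months, and a discharged participant who is later admitted for a breakdown counts under section 5.3.8. What is lost is inpatient time, and neither its length nor the inpatient share is given.

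The second is that rehabilitation centers would appear safer. No between-center safety comparison is planned. Aim 8, on clinical setting, concerns barriers and facilitators, and the by-site report in section 8.2 names recruitment, exclusions and drop-outs, with other information only if needed. Nor do the criteria in section 6 for proceeding to a phase III trial use the SAE rate.

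**Conclusion.** The gap in the definition is real, and its severity is minor. As written, an emotional breakdown in a participant already in hospital that prolongs the stay, without psychiatric-ward admission, suicide attempt or death, is not an SAE under section 5.3 or 5.3.8. The direction of the effect is clear: if such events occur, the SAE count is too low by that number. Its size cannot be estimated from the protocol.

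The conclusion rests on the plain reading that a person already in hospital cannot be newly hospitalized by the event, and on the possibility, permitted by the text, that some participants are inpatients at or after the conversation. It needs no assumed inpatient share or event rate.

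**What to change.** Replace the wording in sections 5.3 and 5.3.8 with one identical SAE definition. Its hospitalization component should cover an emotional breakdown that results in hospitalization, in prolongation of an existing hospitalization, or in transfer to a psychiatric ward; suicide attempt and death stay as they are. This also removes the present disagreement between the two sections over which admissions count. Add a CRF field for inpatient or outpatient status at the time of each event, so that SAEs can be read by setting.

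The cost is one clause in a protocol amendment and one CRF field, with no added burden for participants. The SAE rate may become slightly less favourable. One limit remains: a crisis managed on the same ward without lengthening the stay would still be an AE only, and the definition should say so openly so that sites classify it alike.

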#### **5.2.5 ACP conversation**

The ACP conversation involves the pwPMS, the ACP-trained physician involved in his/her care and, when applicable, the SO. In addition, if the pwPMS agrees, the non-physician ACP-trained HP at the center will participate.

*The first conversation* takes place in a dedicated room at the center, and is audio-recorded. A one-hour slot is reserved for the conversation, and in the case a SO participates it is envisaged that there will be a session closed to the SO, followed by an open session.

About one week before the scheduled first ACP conversation, reminder emails (or phone calls) are sent to pwPMS/SOs. At the end of the first ACP conversation, the physician invites the pwPMS (when applicable the SO) to complete the T1 follow-up assessment within one week. The physician completes the QOC-Doc immediately after the ACP conversation terminates.

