#### **5.2.6 Follow-up assessments (T1, T2)**

The pwPMS completes the questionnaires by one week (T1, assessment time of about 20 minutes) and six months after (T2, assessment time of about 30 minutes) the ACP conversation. The SO completes the questionnaires/instruments (T1, assessment time of about 20 minutes). All the questionnaires are self-completed using the trial platform, except the QOC and the QOC-SO. These questionnaires, originally envisaged as being self-completed, resulted emotionally taxing in the cognitive debriefing sub-study (section 5.3.9). Consequently, an independent, trained interviewer will administer the QOC and the QOC-SO in a phone interview. Before the interview, the interviewer will be notified whether, in the first ACP conversation, EOL care was discussed, or not. If not discussed, the nine QOC/QOC-SO items on communication about EOL care (section 5.3.4) will be skipped (adaptive administration).

In the event the pwPMS/SO have difficulties in using the trial platform, the independent interviewer will administer all the questionnaires/instruments in scheduled telephone interviews.

About one week before the T2 assessment, reminder emails (or phone calls) are sent to pwPMS.

The physician completes the questionnaire (T1, QOC-Doc) and the CRF using the trial platform.

He/she records on the platform the date, duration, participants, and mode (face to face, teleconference or on the telephone) of subsequent ACP conversations that occur during follow-up.

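### Apart from a HADS rise, the only listed non-serious adverse event is contact with the patient's referring physician, so non-serious distress in significant others has no other route into the count

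*Protocol*

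**What the plan says.** Section 5.3 explains why safety is tracked: "since a study-related increase in emotional burden can't be excluded". Section 5.3.8 undertakes to monitor the safety of participants, has the site record AEs, and introduces the list with "AEs will include the following". Two items follow:

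- (a) "any contact to the patient referring physician due to the occurrence of emotional problems during the study";
- (b) an increase of at least 20% "in the HADS Anxiety or/and depression score".

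Serious AEs (SAEs) are defined separately, in section 5.3.8 as "an emotional breakdown resulting in hospitalization, suicidal attempt, or death" and in section 5.3 as "admission to psychiatric ward, suicide attempt, death".

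Four other places bear on how this list works:

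- **Who delivers the intervention.** Section 5.2.5: "The ACP conversation involves the pwPMS, the ACP-trained physician involved in his/her care and, when applicable, the SO". Section 5.1 reserves the one-hour slot for the referring physician.
- **Who is a participant.** Section 5.2.7 counts both patients and SOs.
- **Who completes what.** In Tables 1 and 2, HADS is a patient measure at T0, T1 and T2. SOs complete the ZBI at T0, T1 and T2 and the QOC-SO at T1.
- **Who speaks to participants at T1.** Section 5.2.6: "an independent, trained interviewer will administer the QOC and the QOC-SO in a phone interview". The change was made because debriefing had found these questionnaires emotionally taxing.

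Objective 5 in section 3 is to estimate how often SAEs and AEs occur over the six months.

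**The concern.** Every listed AE that is neither serious nor based on HADS depends on contact with one clinician, and that clinician delivered the intervention. Someone distressed by the conversation may well turn to another person: the center's psychologist or nurse, a family doctor, an emergency department. None of these contacts meets criterion (a).

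The gap is widest for SOs. They are participants, they may sit in the conversation, and they answer a questionnaire that the protocol itself found taxing. Yet the only listed route for their non-serious distress runs through someone else's doctor.

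Objective 5 is at stake, and with it the safety information that feeds the decision on a randomized trial. With a single arm, no comparison group would reveal weak ascertainment.

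**Working it through.** The plan states no figure for AE ascertainment, so there is nothing to reproduce. The check follows each kind of event through the stated criteria, then asks how much criterion (b) recovers for patients.

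**Step 1. Routes into the AE or SAE count**

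| Event | Criterion (a) | Criterion (b) | SAE definition |
|---|---|---|---|
| Patient, serious | not needed | not needed | yes |
| Patient, non-serious, taken to referring physician | yes | if HADS rises at T1 or T2 | no |
| Patient, non-serious, taken elsewhere | no | if HADS rises at T1 or T2 | no |
| SO, serious | not needed | not available | yes (wording not limited to patients) |
| SO, non-serious, reaches patient's physician | yes (caller not restricted) | not available | no |
| SO, non-serious, taken elsewhere | no | not available | no |

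The last row has no route at all. The ZBI does not fill it: section 5.3.6 describes it as a burden measure, and section 5.3.8 attaches no AE to it.

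**Step 2. How sensitive criterion (b) is for patients**

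Inputs: each HADS subscale runs from 0 to 21 in whole points (section 5.3.7), and the trigger is a rise of at least 20% (section 5.3.8). The section does not name the reference score; T0 is assumed here. For a baseline b, the smallest qualifying rise d is the smallest whole number with d / b ≥ 0.20, subject to b + d ≤ 21.

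| Baseline b | Smallest qualifying rise d | Check at the top of the band |
|---|---|---|
| 0 | undefined | percentage change from zero |
| 1–5 | 1 | 1/5 = 20% |
| 6–10 | 2 | 2/10 = 20% |
| 11–15 | 3 | 3/15 = 20% |
| 16–17 | 4 | 3/17 = 17.6% fails; 4/17 = 23.5% qualifies |
| 18–21 | cannot be met | already at 18: 18 × 1.2 = 21.6, above 21 |

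From a baseline of 1 to 15, a rise of one to three points on either subscale makes the patient an AE case wherever help was sought.

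**Step 3. What still escapes for patients**

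HADS is taken within one week of the conversation and then at six months. Distress taken to another professional is missed by both criteria if it does not show at T1 or T2, for example because it arises after T1 and settles before T2. It is also missed if HADS is not completed, or if neither subscale can meet the rule because its baseline is 0 or 18 to 21.

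**Step 4. Size**

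Write s for the share of distress-related contacts that go to the referring physician. Criterion (a) then records s times the true number of such contacts. The documents give neither s nor the true number, so s may lie anywhere from 0 to 1. Some of the patients missed by (a) are recovered by (b), in an unknown proportion. For SOs nothing is recovered by (b).

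**The case against.** The strongest reply is that the list is not closed. It is introduced as what AEs will include, and section 5.3.8 opens by saying that a thorough monitoring plan is still to be developed. Sites record AEs, not only the delivering physician, and the protocol nowhere bars the telephone interviewer from passing on distress. Criterion (a) does not limit who makes the contact, so an SO's call counts, and an SO who attended the conversation has met that physician. SO experience is also explored through the ZBI and the qualitative interviews.

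Much of this stands. The exclusive reading is an inference, though a reasonable one: no other AE is named, no reporting route from the interviewer is stated, and sites will apply what is written. The ZBI and the interviews describe experience but add nothing to the AE count.

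A reader might go further and infer that patient distress taken elsewhere is generally lost. The documents do not support that, because HADS at T1 and T2 is a low-threshold second route that does not depend on where help was sought. A reader might also infer that the AE rate is biased in favour of the intervention. That is not shown for patients: a trigger that can fire on one point may count ordinary fluctuation as AEs, which pulls the total upward while criterion (a) pulls it downward.

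**Conclusion.** The point holds in a limited form. As the criteria are written, non-serious emotional distress in SOs enters the AE count only if it reaches the patient's referring physician. A low SO count under objective 5 could not be distinguished from failure to detect. For patients the gap is smaller: distress taken to another professional and not visible on HADS at T1 or T2.

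The undercount cannot be sized from the documents. Any number obtained by multiplying an assumed true rate by an assumed share s would only return those assumptions. The direction of error is downward for SOs and for criterion (a) taken alone; for the patients' total AE count it is uncertain. SAEs are not affected, since neither definition requires contact with the physician and neither is worded as patient-only.

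This rests on treating the two listed items as the working AE definition and on T0 as the HADS reference. It is an improvement worth making, not a flaw that undermines the pilot.

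**What to change.** In section 5.3.8:

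1. Reword (a) as: any contact by a pwPMS or SO with any health professional because of emotional problems since the last assessment.
2. Ask this as one yes/no question in the T1 telephone interview that already takes place, and on the T2 platform form, for both patients and SOs.
3. State that the interviewer reports a yes to the site for AE recording.
4. Report AEs separately for patients and SOs.

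The T2 question needs a T2 form for SOs. Tables 1 and 2 provide one, with the ZBI at T2, but section 5.2.6 mentions only T1 for SOs and sends T2 reminders to patients only. These should be aligned.

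The cost is one added question, a wording change and AE counts that may be slightly higher. At T2 the answer relies on recall over about six months. No extra staff or visits are needed.

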### 3. AIMS

The present study describes the second phase of the *ConCure-SM* project. The objectives of this pilot and feasibility study are as follows:

1. To determine how many people accept the invitation to participate in the study.
2. To determine how many participants receive the intervention.
3. To estimate recruitment and refusal rates, and 6-month follow-up rates.
4. To estimate ACP completion during the 6-month follow-up (primary study outcome).
5. To estimate occurrence of serious adverse events (SAEs) and adverse events (AEs) during the 6-month follow-up.
6. To assess, qualitatively, the acceptability of the recruitment processes, assessments, intervention delivery and secondary outcome measures with key stakeholders.
7. To measure changes in secondary outcome measures.
8. To explore the barriers and facilitators to implementing ACP in pwPMS, and the influence of the clinical setting.
9. To inform the sample size estimation for a subsequent RCT, should this be feasible.

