### 5.2.7 Withdraw

Participants (pwPMS, SOs) will be free to withdraw from the study at any time, without giving reasons and with no risk of prejudicing future care. Study personnel will make every effort to obtain, and record, information about the drop out reasons.

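### Section 5.3.8 does not link drop-out reasons to the adverse event definition, so a patient who withdraws in distress before any post-baseline HADS can go uncounted

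*Protocol*

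**What the plan says.** Protocol section 5.3 gives the reason for safety monitoring: "since a study-related increase in emotional burden can't be excluded". Objective 5 in section 3 is "To estimate occurrence of serious adverse events (SAEs) and adverse events (AEs) during the 6-month follow-up".

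Section 5.3.8 defines the events. A serious adverse event is an "emotional breakdown resulting in hospitalization, suicidal attempt, or death". AEs are said to include (a) "any contact to the patient referring physician due to the occurrence of emotional problems during the study" and (b) an increase of at least 20% "in the HADS Anxiety or/and depression score". AEs are recorded by the site. Withdrawal because of distress appears in neither definition.

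Section 5.2.7 lets participants leave "without giving reasons and with no risk of prejudicing future care", and adds: "Study personnel will make every effort to obtain, and record, information about the drop out reasons". Section 8.2 lists the reason for drop-out among the data sent to the DSMC before each meeting, overall and by site.

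HADS is taken at T0, T1 and T2 (Tables 1 and 2). T1 falls within one week of the first conversation and T2 six months later (5.2.1). Also at T1, an independent interviewer gives the QOC by telephone, because it "resulted emotionally taxing in the cognitive debriefing sub-study" (5.2.6).

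**The concern.** Emotional harm is the safety question of this study, and leaving is a plausible reaction to it. Both AE routes depend on something that a leaver may not provide: contact with one particular physician, or a further questionnaire. The reason for leaving is collected, but it is handled as retention information. If some patients leave because of distress and reach neither route, the AE proportion is too low. The error runs in one direction, towards the intervention looking safe. Preliminary assessment of safety is part of the study's stated aim (section 1), so this figure will be read as a main result.

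**Working it through.** **The plan's own figures.** The protocol gives no expected AE rate. The relevant figures are in 5.5.1: 35 patients, raised by 15% for drop-outs or incomplete data to 40. Check: 35 × 1.15 = 40.25 and 35 / 0.85 = 41.2, so 40 is close to either calculation. A 15% loss from 40 is 0.15 × 40 = 6, leaving 34.

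**Which leavers are counted.** Consider a patient who withdraws because of distress:

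| Situation | Route (a) | Route (b) | AE? |
|---|---|---|---|
| Tells the referring physician | met | not needed | yes |
| Has given a T1 HADS that rose by at least 20% | not needed | met | yes |
| No post-baseline HADS; tells only the interviewer or non-physician staff | not met | cannot be met | no, although the reason is recorded |
| No post-baseline HADS; gives no reason to anyone | not met | cannot be met | no, and no reason is recorded |

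The third row is the gap: the information exists but does not reach the AE count. The fourth row cannot be repaired by any definition and can only be disclosed. One variant is close to the third row. The order of HADS and QOC within T1 is not fixed, so a HADS completed before the QOC interview cannot show distress that the interview caused.

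**Size.** Let *x* be the patients with an AE under (a) or (b), and *k* the distress withdrawals that neither route catches. Over all 40 recruited, the reported proportion is *x*/40 and the full one is (*x* + *k*)/40. The shortfall is *k*/40, whatever *x* is:

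- *k* = 0: 0 points
- *k* = 1: 1/40 = 2.5 points
- *k* = 2: 2/40 = 5.0 points
- *k* = 3: 3/40 = 7.5 points
- *k* = 6: 6/40 = 15.0 points

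If the proportion were instead taken over the 34 who remain, the shortfall would be (*x* + *k*)/40 − *x*/34, which never exceeds *k*/40. For example, with *x* = 3 and *k* = 3, 3/34 = 8.8% is reported against 6/40 = 15.0%, a gap of 6.2 points.

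For scale, three such events and no others would be 3/40 = 7.5% (exact 95% CI 1.6 to 20.4%).

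**Wider loss.** Section 6 requires retention above 70%. The smallest number that satisfies this is 29 of 40 (72.5%), so up to 11 could leave. If all 11 fell in the gap, the shortfall would be 11/40 = 27.5 points. This is an outer bound, not an expectation.

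**The case against.** A reader might infer that a distressed leaver is never an AE, gives no later HADS, and that the safety result therefore omits the patients most likely to have been harmed. The protocol does not support that.

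- **The AE list may not be closed.** Section 5.3.8 says what AEs include, and it announces a fuller safety monitoring plan that is not shown. This stands as a limit on the claim. An open list, however, lets sites classify the same event differently, and a stated rule would settle that.
- **Route (a) is broad.** The physician who recruits, takes consent, holds the conversation and completes the CRF is involved in the patient's care (5.2.3 to 5.2.6), and any contact counts. Some, perhaps most, distressed leavers would be caught. The gap needs a patient who tells only someone else.
- **A HADS is due soon.** T1 comes within a week of the conversation. A patient who leaves after T1 loses only the T2 HADS, and one upset by the QOC interview may already have completed the T1 HADS.
- **Oversight is not blind.** Drop-out reasons reach the DSMC, whose remit includes safety data. What can be missing is an entry in the AE count.
- **The phase III decision has no AE threshold.** Section 6 sets none, and withdrawals already count against retention. The effect is on the reported safety estimate, not on a formal decision rule.
- **The illustration is assumption.** The 15% covers incomplete data as well as drop-outs, and the protocol gives no share leaving for distress. An example with no other AE is also unlikely: 20% of a baseline subscale score of 5 is 1 point, so a one-point rise qualifies for any non-zero baseline up to 5.

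The multiple imputation and intention-to-treat statements in 5.5.2 do not close the gap. The protocol does not say that imputation applies to AEs, and under the usual missing-at-random assumption it would not recover loss that depends on unobserved distress.

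**Conclusion.** The point holds in a limited form. No rule in 5.2.7, 5.3.8 or 8.2 turns a recorded drop-out reason of emotional distress into an AE. A patient who leaves before giving a post-baseline HADS, and who reports the distress only to the interviewer or non-physician staff, is uncounted under objective 5, and the bias runs towards safe.

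The size is unknown. The range of 0 to 15 percentage points assumes that the planned 15% loss consists entirely of withdrawals, that 0 to 6 of the 40 leave for distress, and that none of them is caught by route (a) or a T1 HADS. The upper end is therefore extreme. It is plausible that these are the patients most affected, but nothing in the protocol shows it. No two sections contradict each other. This is a missing link between two records, and it should be closed because the information is already being collected.

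**What to change.** - **In 5.3.8**, count as an AE any withdrawal, or early ending of a conversation or interview that has begun, whose recorded reason is emotional distress, whoever received the report (physician, other health professional or interviewer).
- **In 5.2.7**, require such a reason to be entered as an AE on the eCRF.
- **In reporting**, give the AE proportion over all recruited patients. Show beside it the number who withdrew without a stated reason and the number with no post-baseline HADS.

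Do not count refusal to start the conversation. Section 2 says that a wish not to engage should be respected, and an event before the conversation cannot be attributed to it, while 5.3.8 asks for attribution to the intervention.

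The cost is two short additions to the text, one link in the eCRF and two extra counts in the report. The downside is a somewhat higher AE count.
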